## Abstract

**Background:**

Assessment of disease activity is a critical component of tight-control, treat-to-target treatment strategies of rheumatoid arthritis (RA). Recently, the HandScan has been validated as a novel method for objectively assessing RA disease activity in only 1.5 min, using optical spectral transmission (OST) in hands and wrists. We describe the protocol of a randomized controlled clinical trial (RCT) to investigate whether HandScan-guided treatment aimed at ‘HandScan remission’ (HandScan arm) is at least as effective as and more cost-effective than clinically guided treatment aimed at ACR/EULAR 2011 Boolean remission (DAS arm).

**Methods/design:**

The study is a multi-center, double-blind, non-inferiority RCT of 18 months duration. Patients ≥ 18 years with newly diagnosed, disease-modifying antirheumatic drug (DMARD)-naïve RA according to the ACR 2010 classification criteria, will be randomized to the DAS arm or the HandScan arm. The efficacy of the arms will be compared by evaluating Health Assessment Questionnaire (HAQ) scores (primary outcome) after 18 months of DMARD therapy, aimed at remission. The equivalence margin in HAQ scores between study arms is 0.2. Secondary outcomes are differences in cost-effectiveness and radiographic joint damage between treatment arms. The non-inferiority sample size calculation to obtain a power of 80% at a one-sided *p* value of 0.05, with 10% dropouts, resulted in 61 patients per arm. In both arms, DMARD strategy will be intensified monthly according to predefined steps until remission is achieved; in both arms DMARDs and treatment steps are identical. If sustained remission, defined as remission that persists consistently over three consecutive months, is achieved, DMARD therapy will be tapered.

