### Statistical analyses

#### Sample size

Sample size was calculated for the primary outcome, HAQ score, and the primary analysis of the non-inferiority design using two-sample *t*-tests and data from the CAMERA-II trial: mean (SD) HAQ score at 18 months 0.38(0.4) [15]. An equivalence margin of 0.2 in HAQ scores between study arms was considered clinically acceptable. A sample size of 51 per group was calculated to obtain a power of 80% at a one-sided *p* value of 0.05. Taking into account 10% drop-out, total sample size was set at 112 patients.

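### The abstract's 61 patients per arm (122 in total) contradicts the 112 in total of the Sample size section and does not follow from 51 per group with 10% dropout

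*Protocol article*

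**What the plan says.** The article gives the result of the sample size calculation twice.

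- **Abstract, Methods/design.** The margin is 0.2 HAQ points, power 80%, one-sided 0.05. The calculation, "with 10% dropouts, resulted in 61 patients per arm". At two arms that is 122 patients.
- **Statistical analyses, Sample size.** The calculation is for "the primary analysis of the non-inferiority design using two-sample *t*-tests", with an SD taken from an earlier trial ("mean (SD) HAQ score at 18 months 0.38(0.4"). The margin is the same: "An equivalence margin of 0.2 in HAQ scores between study arms was considered clinically acceptable". The test level is the same: "at a one-sided *p* value of 0.05". The result before dropout is 51 per group ("A sample size of 51 per group was calculated to obtain a power of 80" per cent). Then: "Taking into account 10% drop-out, total sample size was set at 112 patients".

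The main Methods/design section sets 1:1 randomisation, so 112 is 56 per arm. The article nowhere mentions a second calculation, a change of target, or a different dropout allowance. The Trial status section says that recruitment is under way.

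**The concern.** Both figures claim to be the number to randomise once 10% dropout is allowed for. The difference is therefore not one of evaluable against enrolled patients. One document gives two enrolment targets, ten patients apart, from what it presents as one calculation.

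The target decides when recruitment closes. With two published values, closing at 112 meets the Sample size section and falls 10 short of the abstract, while going on to 122 meets the abstract and exceeds the Sample size section. In a non-inferiority trial it should be beyond doubt that the stopping point was fixed in advance.

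There is a second possibility. If 61 per arm is the intended number, the 10% dropout printed in both places may not be the allowance actually used, and a planning assumption is then misreported.

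**Working it through.** **Inputs**

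| Input | Value | Source |
|---|---|---|
| Margin | 0.2 HAQ points | Abstract; Sample size |
| SD | 0.4 | Sample size |
| Level | 0.05, one-sided | Abstract; Sample size |
| Power | 80% | Abstract; Sample size |
| Dropout | 10% | Abstract; Sample size |
| Allocation | 1:1 | Methods/design |
| True difference | 0 | Assumption; the article states no other value |

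**Step 1: reproduce the 51 per group.**
Normal approximation: n = 2 × (z₀.₉₅ + z₀.₈₀)² × SD² / margin² = 2 × (1.645 + 0.842)² × 0.16 / 0.04 = 49.5, so 50 per group.
Two-sample t-test with the noncentral t distribution (df = 2n − 2, noncentrality = 0.2 / (0.4 × √(2/n))): n = 50 gives 79.9% and n = 51 gives 80.6%. The smallest n reaching 80% is 51. The stated figure reproduces.

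**Step 2: from 51 per group to the 112 of the Sample size section.**
- Multiplying by 1.1: 102 × 1.1 = 112.2, about 112 (56 per arm).
- Dividing by 0.9: 51 / 0.9 = 56.7, so 57 per arm and 114 in total.

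The two conventions differ by two patients (1.8%). With exactly 10% loss, 112 × 0.9 = 100.8 evaluable, or 50.4 per arm. That lies between the two t-test results above, at about 80.2%.

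**Step 3: from 51 per group to the 61 per arm of the abstract.**
- Neither convention in Step 2 gives 61; they give 56.1 and 56.7.
- Implied loss if 51 of 61 remain: 1 − 51/61 = 16.4%.
- An added allowance of 20% would come close (51 × 1.2 = 61.2), but both places state 10%.
- With 10% loss, 61 × 0.9 = 54.9 evaluable per arm, which gives about 83.1% power by the t-test rather than 80%.

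**Step 4: other designs that might explain 61 (per group, before dropout).**
- One-sided 0.025: 63 (normal) or 64 (t-test).
- 90% power at one-sided 0.05: 69 (normal).
- Two one-sided tests for equivalence, 80% power: 69 (normal).

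All already exceed 61 before any dropout is added.

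**Side by side, with 10% loss**

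| Randomised | Per arm | Evaluable per arm | Power (t-test) |
|---|---|---|---|
| 112 (Sample size section) | 56 | 50.4 | about 80.2% |
| 122 (abstract) | 61 | 54.9 | about 83.1% |

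**The case against.** The strongest reply is that the Sample size section is the operative text. It gives the inputs, the evaluable number and a total, and these agree with one another. The abstract is a summary line. No interim efficacy analysis is described, and the early look under Patient safety counts arm switches and protocol violations in the first 20 patients, which does not depend on the target. Power is about 80% or better at either size, and margin, level and analysis are untouched. On this view it is a slip in the abstract.

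Most of that stands, and it limits the consequence. It does not remove the contradiction. Both statements are intact running prose. A full protocol or analysis plan that is not shown could not make both correct, because the complaint is about two incompatible statements and not about an omission. Nor does the article say that its abstract is the figure in error, so the sponsor has to confirm it.

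A reader might go further and say that 112 is wrong too, because dividing by 0.9 gives 114. The document does not support that. The Sample size section names no inflation formula, 112 is what multiplying by 1.1 gives, and the two-patient difference leaves power at about 80%. In addition, the 51 comes from an unadjusted t-test, whereas the primary analysis adjusts for baseline HAQ and other covariates. To the extent that baseline HAQ predicts the 18-month score, that adjustment reduces residual variance, so a shortfall of this size has no practical meaning.

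**Conclusion.** The contradiction is real: 122 against 112 randomised patients, a gap of 10 (10/112, about 9%), from the same stated power, level, margin and dropout. The unexplained figure is the abstract's 61 per arm. The 51 per group reproduces, and the 112 is consistent with it.

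A reader might infer that the trial is underpowered. It is not, materially, at either size on its own inputs. The defect is an unclear enrolment target and, if 61 was intended, a misstated dropout allowance.

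This rests on SD 0.4, a true difference of 0 and the unadjusted t-test named in the Sample size section. The abstract does not restate the SD; I take it to report the same calculation. The mismatch between 61 per arm and 112 in total needs none of these assumptions.

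**What to change.** State one randomised target, per arm and in total, in both the abstract and the Sample size section, and name the inflation method. The sponsor can settle which figure applies from the full protocol (version 3.0, cited under Trial registration).

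- If 112 is the target: correct the abstract to 56 per arm, 112 in total. Nothing in the Sample size section has to change. A move to 57 per arm (114) is not needed.
- If 61 per arm is the target: state the dropout allowance or other input that produces it, and correct the 112 and the 10% wherever they appear.

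The correction is to text only. Aligning the abstract with the Sample size section requires no recalculation and no extra patients beyond the 112.

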**Discussion:**

The study protocol and the specifically designed decision-making software application allow for implementation of this RCT. To test a novel method of assessing disease activity and comparing (cost-)effectiveness with the contemporary method in treat-to-target DMARD strategies in early RA patients.

**Trial registration:**

Dutch Trial Register, NTR6388. Registered on 6 April 2017 (NL50026.041.14). Protocol version 3.0, 19-01-2017.

**Electronic supplementary material:**

The online version of this article (10.1186/s13063-019-3285-8) contains supplementary material, which is available to authorized users.

## Background

Rheumatoid arthritis (RA) is a chronic autoimmune disease with polyarthritis, frequently leading to joint damage and physical disability, especially if not treated adequately as soon as possible after diagnosis. Treatment in the first months is more effective than if the same treatment is applied later in the course of disease [1]. Early and intensive (tight-control) treatment of RA with disease-modifying antirheumatic drugs (DMARDs) has significantly improved RA outcome [2, 3]. The aim of tight-control treatment, i.e., tailoring treatment strategy to the disease activity of individual patients, is to achieve a predefined level of low disease activity, preferably remission (treat-to-target), within a reasonable period of time.

For tight-control and treat-to-target treatment strategies for the treatment of RA, typically frequent disease activity assessment is applied using the Disease Activity Score (DAS), a composite score of an acute phase reactant, such as C-reactive protein (CRP), patient global assessment (PGA), and swollen and tender joint counts (SJC and TJC, respectively) of 28 or 44 joints. Although commonly used in research and daily clinical practice, assessment of the DAS is rather time-consuming and subjective, and the DAS is only validated on the group level [4]. However, fast, objective, and easily implementable tools to assess arthritis and disease activity are lacking [5]. The HandScan (Hemics BV), using optical spectral transmission (OST), objectively measures the reduced transmission of light through joint tissues in the presence of inflammation (e.g., synovitis, tenosynovitis) [6, 7]. HandScan results reflect disease activity, correlating moderately with DAS28 (r = 0.42, *p* = 0.001) [6]. Moreover, HandScan correlates moderately with ultrasound (US) assessing synovial inflammation of hand and wrist joints (Spearman’s correlation coefficient, ρ = 0.54, 95% CI 0.28 to 0.73, *p* < 0.01), while DAS28 did not correlate with these US results (ρ = 0.06, 95% CI − 0.26 to 0.36, *p* = 0.71) [7]. Test-retest reliability of the HandScan was excellent at both the patient level (ICC = 0.86, 95% CI 0.76 to 0.92, *p* < 0.001) and joint level (ICC = 0.76, 95% CI 0.73 to 0.79, *p* < 0.001) [7]. In addition, HandScan has proven to be user-friendly—i.e., an assistant without medical background can operate the device—and fast (it provides the inflammation score within 1.5 min).

The aim of this study protocol, designed according to the SPIRIT 2013 Checklist (Additional file 1), was to determine the applicability of the HandScan in tight-control and treat-to-target treatment strategies of early RA patients. To facilitate this, a specifically designed decision-making software application was developed, allowing for double-blind comparison of HandScan-guided treatment with the contemporary method of DAS-guided treatment.

## Methods/design

This is an investigator-initiated, multi-center, double-blind non-inferiority randomized controlled trial (RCT) of 18 months duration. Patients will be randomized (1:1) to a HandScan-guided treatment aimed at HandScan remission (HandScan arm) or a clinically DAS-guided treatment aimed at ACR/EULAR 2011 Boolean remission (DAS arm). The study is performed at six departments of rheumatology in the Netherlands, the University Medical Center Utrecht (UMCU), and five non-university hospitals: Meander Medical Center Amersfoort, Noord West Ziekenhuizen Alkmaar, Máxima Medisch Centrum Eindhoven, and Gelre Ziekenhuizen Apeldoorn. The study has been approved by the Ethical Committee of the University Medical Center Utrecht, Utrecht, The Netherlands on April 6, 2017 (NL50026.041.14), and has been registered in the Dutch Trial Register (NTR6388). Privacy of patients will be protected according to the General Data Protection Regulation, using anonymized data.

### Objectives and primary and secondary outcomes and their rationale

The overall aim of the study described in this protocol is to demonstrate clinical efficacy and cost-effectiveness of the HandScan arm compared to the DAS arm, with identical treatment and treatment steps in both arms. The primary outcome is the change in Health Assessment Questionnaire (HAQ) score from baseline to 18 months, reflecting both actual disease activity and physical disability as a measure for cumulative past disease activity [8]. We chose not to use DAS remission or the Boolean remission criteria with the components of DAS as primary outcome, first, because this would probably favor the DAS arm of our trial over the HandScan arm and, second, because DAS-based remission criteria have a relatively high risk of false negative classification of remission. This is caused by high scores on PGA and TJC in case of concomitant soft tissue rheumatism, fibromyalgia, or other non-inflammatory pain of chronic pain syndrome [9].

Secondary outcomes are the change in HAQ score over time, cost-effectiveness, based on customized cost questionnaires (including direct and indirect costs), and radiographic damage of hand and wrist joints, assessed using a newly developed fully automated radiographic scoring system of joint width of hand and wrist joints [10], as well as the conventional Sharp van der Heijde (SvdH) score of joint width and erosions of hands, wrists, and feet [11].

### Patients

Patients ≥ 18 years with newly diagnosed DMARD-naïve RA according to the ACR/EULAR 2010 classification criteria [12] will be eligible for this study. Detailed selection criteria are shown in Table 1.

**Table 1 Tab1:** Selection criteria

Inclusion criteria	
• Early (< 1 year) RA, fulfilling 2010 ACR/EULAR criteria	
• Age ≥ 18 years	
• Ability and willingness to give written informed consent	
• Ability to comply with the study protocol	
Exclusion criteria	
• Significant visual deformations of hands or fingers (impeding HandScan analysis)	
*Other (joint) disease*	
• Concomitant or current inflammatory joint disease other than RA	
• Porphyria (HandScan risk analysis).	
*Drug-specific*	
• Contraindication for methotrexate or prednisolone	
• Glucocorticoids used for RA < 6 weeks prior to baseline (NB, inhaled glucocorticoids are allowed)	
• Previous treatment with any (biological) DMARD that is used in the treatment of RA	
• Treatment with any investigational agent within 4 weeks or period of five half-lives, whichever is longer, before screening	
• Patients using photodynamic therapy medication (HandScan risk analysis)	
*General medical*	
• Pregnancy or breast-feeding	
• History of alcohol or substance abuse within the 6 months prior to screening. Alcohol abuse is defined as more than 3 units per day	
• Neuropathies or other painful conditions that might interfere with pain evaluation	

All participating patients provide written informed consent, according to the ethical principles from the Declaration of Helsinki. At the screening visit, informed consent is signed by the patient and research/rheumatology nurse or investigator, and selection criteria are checked.

### Randomization

Randomization lists per center will be prepared at UMC Utrecht, using *nQuery Advisor* in permuted blocks of 4; randomization lists are safeguarded at the UMC Utrecht. Randomization data will be incorporated in the decision-making software application that is used in each of the institutes. This way, on-site research staff, patients, and sponsor trial personnel will remain blinded to treatment strategy. A patient will be allocated to the HandScan or DAS arm, as soon as baseline clinical data are entered into the software application. A patient-specific study number and the year of birth will function as identifiers. Unblinding will not be necessary as both arms receive identical medication in an open fashion.

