### Implementation of a software application for patient-tailored, tight-control treatment

Although treatment regimens and dosing steps are identical for all patients, actual medication will differ considerably between patients in this study, as the study protocol tailors treatment to every patient in a treat-to-target strategy (Fig. 3). To account for these variations in treatments and to allow for double-blind treatment, a decision-making software application was developed. It uses a data trail (data log) of current and previous patient-specific input to check, e.g., for consistent discordance between remission criteria and prevent drug dosages higher than previous MTD in case of a flare. At each visit, the patient identification number, year of birth, and parameters for both clinically and HandScan-assessed disease activity will be entered into the application. Based on whether there is remission or not, according to the criteria of the randomized arm, the application will provide the next patient-specific medication step.

The application was developed and tested to conform to the regulations and guidelines for the development of a medical appliance class I and medical software class B (*EN 62304 Medical device software –Software life-cycle processes, EN 62366 Usability, ISO 14971 Medical devices – Application of risk management to medical devices*).

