#### Primary outcome analyses

The primary outcome is HAQ score; the primary analysis is a general linear model, testing HAQ scores at 18 months between the two arms according to intention to treat (ITT), controlling for baseline HAQ, center (stratification factor in the randomization), and the baseline covariates age, gender, disease activity (DAS28), rheumatoid factor, and anti-CCP. The ITT population will include all randomized patients as long as they have taken study medication at least once and at least one efficacy measurement was obtained. Secondary analyses are 1) the primary analysis, but for the per protocol population (i.e., all patients without major protocol violations or a switch between study arms), and 2) a mixed model analysis comparing HAQ scores over time (baseline and 3, 6, 12, and 18 months) between the study arms. In this model we will control for the same covariates as those in the primary analysis. Although this model handles missing data well, if ≥ 10% of data are missing, as a sensitivity analysis data will be analyzed after multiple imputation if data seem to be missing at random.

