## Trial status

The trial started April 4, 2017 and is currently recruiting.

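### Blocks of exactly 4 within each center, disclosed during recruitment, let staff who can infer earlier arms predict some later allocations; undisclosed varying block sizes are a cheap improvement

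*Protocol article*

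**What the plan says.** Under Randomization in the protocol article: "Randomization lists per center will be prepared at UMC Utrecht", "in permuted blocks of 4; randomization lists are safeguarded at the UMC Utrecht". No variation in block size is mentioned. Methods/design gives the ratio: "Patients will be randomized (1:1) to a HandScan-guided treatment aimed at HandScan remission". The Primary outcome analyses section confirms center as the stratum: "center (stratification factor in the randomization". Each block at each center therefore holds two HandScan and two DAS places.

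The same section says that "on-site research staff, patients, and sponsor trial personnel will remain blinded to treatment strategy". The software allocates a patient once the baseline clinical data have been entered, and medication is given openly.

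Under Assessments, every monthly visit includes both the HandScan and the DAS44. The section on the software application has both sets of results entered, and then, using the randomized arm's criteria only, "the application will provide the next patient-specific medication step". The Definitions of remission section sets out both rules in full and says that the HandScan displays its joint scores soon after the scan.

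Trial status says: "The trial started April 4, 2017 and is currently recruiting".

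**The concern.** Keeping the list in Utrecht conceals the next allocation only while earlier allocations in the same block stay unknown. With a known block size of 4, two revealed patients in the same arm settle the rest of the block.

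The article's own description offers a route to earlier arms. Suppose one remission rule is met and the other is not. Advice to intensify or to leave treatment unchanged then shows which rule was applied. The switch to DAS guidance does not hide this, because it acts only after three consecutive discordant visits; the first such visit still follows the randomized arm.

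What is at stake is who is offered entry. The Discussion names reliance on hands and wrists as the HandScan's main drawback. A recruiter who expects a HandScan place next could hold back a patient whose disease is mainly in the feet. This would tend to favor the HandScan arm, which in a non-inferiority trial is the direction of the hoped-for conclusion. The primary model adjusts for baseline HAQ, center, age, gender, DAS28, rheumatoid factor and anti-CCP, but has no term for joint distribution. Blinding after entry cannot undo selection at entry.

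**Working it through.** The article gives no figure for predictability, so there is none to reproduce.

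**Inputs from the article.** Blocks of 4, 1:1, one list per center (Randomization, Methods/design); six departments ("The study is performed at six departments of rheumatology in the Netherlands"); total 112 (Sample size); monthly visits (Assessments); correlation of HandScan with DAS28, r = 0.42 (Background).

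**Assumptions, not in the article.** Discordance per visit of 10% to 50%, independent between visits; mean gap between enrolments at a center of 0.5 to 3 months; the recruiter sees both scores and the advice.

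**1. Ceiling: all earlier arms in the block known.** Of the six possible blocks, the fourth place is always determined, and the third is determined when the first two match (probability 1/3).
- Share certain = (0 + 0 + 1/3 + 1)/4 = 1/3 = 33%.
- Correct when guessing the arm with more places left = (1/2 + 2/3 + 2/3 + 1)/4 = 17/24 = 71%, against 50% by chance.

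**2. Plausible discordance.** Treat the two measures as bivariate normal with r = 0.42 and remission rates p and q. Discordance is p + q − 2 × P(both in remission). With p = q = 0.30, P(both) is about 0.145, so discordance = 0.60 − 0.29 = 0.31. With p and q between 0.10 and 0.50 it runs from about 0.14 to 0.44. This borrows the DAS28 correlation for the Boolean rule and is only a guide.

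**3. Allowing for delay.** All patients start on the same drugs, so nothing shows at allocation, and concordant visits show nothing. In a simulated center of 20 patients, an arm is revealed at the first discordant monthly visit, month 1 at the earliest. Cells give share certain / share of guesses correct:

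| Mean gap (months) | Discordance 10% | 30% | 50% |
|---|---|---|---|
| 0.5 | 0.2% / 51% | 1.0% / 52% | 2.5% / 54% |
| 1 | 0.8% / 52% | 4.1% / 56% | 8.1% / 58% |
| 2 | 2.8% / 55% | 10.4% / 60% | 15.8% / 62% |
| 3 | 4.9% / 56% | 14.8% / 62% | 20.0% / 64% |

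**4. Hand check.** 112/6 = 18.7 patients per center. If accrual took 24 months (assumed), the gap is 24/18.7 = 1.3 months. When the fourth patient of a block enrols, the first three have had about 3, 2 and 1 guided visits. At 30% discordance, the chance that each is revealed is 1 − 0.7³ = 0.66, 1 − 0.7² = 0.51 and 0.30.
- Fourth place certain: (0.66 × 0.51 + 0.66 × 0.30 + 0.51 × 0.30)/3 = 23%.
- Third place certain: (0.51 × 0.30)/3 = 5%.
- Over four places: (0.23 + 0.05)/4 = 7%. The same sum gives about 1% at 10% discordance and 15% at 50%.

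This agrees with the table. At 7%, it is 0.07 × 18.7 = 1.3 patients per center.

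**The case against.** - **Access is not established.** The article says on-site staff stay blinded, notes that an assistant without medical background can run the HandScan, and does not say who enters the data. The full protocol, not shown, may separate these roles. This stands as a limit: the inference is possible on the description given, but not shown to be available to a recruiter.
- **The signal is noisy.** Dose changes for adverse events, and the last rows of Table 2 where the step does not change, blur the advice. Discordance that clusters within patients would generally lower the shares further. This stands too.
- **Motive and means are limited.** Baseline HAQ is in the model, so selection on disability is largely answered. Deferral is hard, since a patient who starts a DMARD meanwhile becomes ineligible, though simply not offering the trial remains possible. Persistently discordant HandScan patients move to DAS guidance anyway. What remains is selection on joint distribution.
- **Fixed blocks contradict nothing in the article.** True; this is a design weakness, not an error.

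A reader might infer that a center can foresee a third of its allocations, or that enrolment has been selective. The documents support neither. The one-third figure needs every earlier arm in the block to be known at each enrolment, and nothing in the article bears on actual enrolment behavior.

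**Conclusion.** The concern holds as a modest, avoidable weakness in allocation concealment. Some allocations could be predicted by staff who see both scores and the advised step. Under the mid-range assumptions (30% discordance, 1 to 2 months between enrolments) that means about 4% to 10% certain, or 0.04 × 112 = 4 to 0.10 × 112 = 11 patients if every center had such a person, with 56% to 60% of guesses right. Over the full assumed range it is 0.2% to 20% certain and 51% to 64% right. The 33% and 71% are upper bounds. Discordance, accrual and access to the scores are all assumptions. The remaining risk is selective enrolment on disease outside the hands and wrists, for which the primary model has no direct adjustment.

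**What to change.** For allocations not yet made, load new center lists with randomly varying block sizes, for example 2, 4 and 6. Keep stratification by center, do not disclose the sizes to sites, and record the date of change.

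The gain is in certain predictions. Larger fixed blocks would help less: with all earlier arms known, a known block of 6 still gives 25.0% certain and 68.3% correct guesses, and a block of 8 gives 20.0% and 66.6%. With sizes 2, 4 and 6 equally likely and in unknown order, a simulated center of 20 patients gives about 4% certain even if all earlier arms are known. Best guesses hardly change, because guessing the arm that is behind needs no block size: (2 × 0.75 + 4 × 0.708 + 6 × 0.683)/12 = 70%. The change therefore does not close the route by which arms are inferred. It removes most of the certainty that this route gives.

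The cost is a short amendment, loading and checking a list inside tested medical software, and a possible within-center imbalance of at most 3 patients instead of 2. Any table of baseline features (HAQ, joint distribution, HandScan score) by arm and block position should wait until database lock or be made by an independent unblinded person, because trial personnel are to stay blinded.
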